## 1. Scope

This Statistical Analysis Plan (SAP) describes the outcomes and analyses for the long term follow up of the Auckland Steroid Trial (AST). In this plan the mothers who participated in the AST are referred to as the F0 generation, their children the F1 generation and their grandchildren the F2 generation. This SAP concerns the fifty-year follow-up of children (F1 generation) of the participants of the Auckland Steroid Trial. This follow-up study was conducted as part of the AnteNatal Corticosteroids Health Outcomes Review (ANCHOR) Study. Outcomes of the mothers who participated in the Auckland Steroid Trial (F0 generation) and their grandchildren (F2 generation) are outside of the scope of this analysis plan.

## 2. Study information

### 2.1. Aim

- To determine if antenatal corticosteroids, given to women at risk of preterm birth, have long term impacts on the health of offspring (F1).

### 2.2. Study hypothesis

Antenatal corticosteroids reduce neonatal mortality and morbidity without long-term adverse impacts on health and social outcomes in offspring (F1).

## 3. Background: The Auckland Steroid Trial (1969-1974)

A single centre, two-arm, parallel, randomised double blind placebo-controlled trial comparing treatment with antenatal corticosteroid to placebo for improving rates of respiratory distress syndrome.

### 3.1. Inclusion Criteria

- Women with threatened or planned preterm delivery
- Gestational age at recruitment 24 to <37 weeks
- Women with multiple pregnancies, fetal anomalies, preterm prelabour rupture of membranes, hypertensive disorders of pregnancy and diabetes mellitus were all eligible for inclusion

### 3.2. Exclusion criteria

- Imminent delivery
- Contraindication to corticosteroids

### 3.3. Randomisation, treatment allocation and masking

A random-number table was used to generate the randomisation sequence. This was performed by the chief pharmacist who held the randomisation key. The pharmacy provided numbered, identical drug ampoules that contained either corticosteroids or the control treatment. Women received an intramuscular injection of the allocated treatment, followed by a further intramuscular injection of the same type after 24 hours if delivery had not occurred. The antenatal corticosteroid treatment contained 6 mg of short-acting betamethasone phosphate and 6 mg long-acting betamethasone acetate. The control treatment contained 6 mg cortisone acetate which has a glucocorticoid potency of one seventieth of the active treatment. In October 1972, after 717 women had been enrolled, the dose of the betamethasone and control treatments were both doubled.

### 3.4. Co-interventions

For women in preterm labour, tocolytic therapy was administered in an attempt to delay birth for 48 to 72 hours from the first study injection unless there were signs of fetal distress or

amnionitis. The tocolytic of choice was initially intravenous infusion of ethanol, and changed to intravenous infusion of salbutamol in June 1971 after recruitment of the first 236 women. For women with preterm prelabour rupture of the membranes (PPROM) broad spectrum intravenous antibiotics were administered, typically ampicillin.

### 3.5. 30-year follow up

The Auckland Steroid trial F1 generation were followed up at approximately 30 years of age. Follow up of 534 participants was performed and included questionnaires; clinical assessments of cardiovascular risk factors such as height, weight, blood pressure; blood tests including morning plasma cortisol, plasma lipids, oral glucose tolerance tests with concurrent insulin measurements; DEXA (dual energy x-ray absorptiometry) bone density measurements; spirometry for lung function testing and detailed psychosocial assessments.

## 4. Methods for the ANCHOR Study: follow up of the Auckland Steroid Trial F1

### 4.1. Study design

This study consists of long term follow up of the Auckland Steroid Trial at 50 years comparing outcomes in offspring (F1) for those exposed to antenatal corticosteroid to those exposed to placebo.

Participants were blinded to allocation from randomisation up to 30-year follow up, at which point those participants who wished to have their treatment allocation disclosed were informed by letter. Investigators and all study staff for this 50-year follow up remained unaware of treatment allocation.

Follow up consists of a questionnaire based on the New Zealand Health Survey and consent to accessing routinely collected data from government agencies including the Ministry of Health (including Testsafe), Ministry of Education, New Zealand Qualifications Authority, Accident Compensation Corporation, Ministry of Justice and Statistics New Zealand.

### 4.2. Inclusion Criteria

Participants were eligible for inclusion if they had been born to a participant of the Auckland Steroid Trial and written informed consent was obtained to participate in the study. Participation in the 6-year follow up study or the 30-year follow up study was not a requirement for participation.

### 4.3. Exclusion criteria

Declined participation or unable to obtain informed consent from participant or legal guardian.

## 5. Study outcomes

Outcome definitions and the hierarchical approach to different data sources have been detailed in a supplementary document (S1). This supplemental document may be amended separate to this analysis plan and will be finalised after blinded review of the data with the aim of optimising the validity of outcome definitions. All outcomes for this analysis plan will use one of three denominators as indicated by the following superscript designation:

a Denominator will be all participants whose mothers were randomised in the original trial.

b Denominator will be all participants alive at 28 days of age.

c Denominator will be all participants who consented to this follow-up study with data available for the outcome.

s indicates outcomes for which a separate analysis will be undertaken using only self-reported data (see section 10).

#### 5.1. Primary outcomes

1. Composite of cardiovascular risk factors cs. Any of:
  - Diabetes mellitus or prediabetes
  - Hypertension
  - Dyslipidaemia
2. Age at first major adverse cardiovascular event bs. Earliest of:
  - Age at first admission for myocardial infarction or coronary revascularisation
  - Age at first admission for peripheral vascular disease (acute limb ischaemia or revascularisation)
  - Age at first admission for stroke
  - Age at first heart failure admission
  - Age at cardiovascular death

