#### 5.2. Secondary outcomes

##### **Components of the Primary outcomes**

- Diabetes mellitus or prediabetescs
- Diabetes mellituscs
- Prediabetescs
- Hypertensioncs
- Dyslipidaemiacs
- Age at cardiovascular deathb
- Proportion with cardiovascular deathb
- Age at first admission for myocardial infarction or coronary revascularisationbs
- Age at first admission for myocardial infarctionbs
- Age at first admission for coronary revascularisationbs
- Age at first admission for peripheral vascular disease (arterial thrombosis/embolism or need for revascularisation)bs
- Age at first admission for arterial thrombosis/embolismb
- Age at first admission for peripheral revascularisation procedureb
- Age at first admission for strokebs
- Age at first heart failure admissionbs
- Proportion with at least one admission for myocardial infarction or coronary revascularisationbs
- Proportion with at least one admission for myocardial infarctionbs
- Proportion with at least one admission for coronary revascularisationbs
- Proportion with at least one admission for peripheral vascular disease (arterial thrombosis/embolism or need for revascularisation)b
- Proportion with at least one admission for arterial thrombosis/embolismb
- Proportion with at least one admission for peripheral revascularisation procedureb
- Proportion with at least one admission for strokebs
- Proportion with at least one admission for heart failureb

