### 10. Analysis based on Self-reported Outcomes

An aim of this research program is to compare outcomes based on expert clinical synthesis of administrative and self-reported data and those based on questionnaire responses completed by

each participant. A complementary analysis of the appropriate outcomes indicated in section 5 above by the superscript S (self-reported) will be completed with all participants for those questions which most closely match the outcomes listed in section 5.

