### Supplementary Tables

**Supplementary Table 1 Primary outcomes based on self-reported questionnaire only**

| Outcome | Betamethasone
N = | Placebo
N = | Unadjusted
RR, HR or
mean
difference
(95% CI) | RR, HR or
mean
difference
(95% CI) | P value |
|----------------|------------------------------|------------------------|----------------------------------------------------------------------|-------------------------------------------------------|----------------|
|                |                              |                        |                                                                      |                                                       |                |

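### The self-report mark sits on the full MACE composite, so the planned comparison of data sources for that outcome also mixes endpoint content and population

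*SAP*

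**What the plan says.** - Section 5 assigns every outcome one of three denominators. Mark b is everyone alive at 28 days of age. Mark s "indicates outcomes for which a separate analysis will be undertaken using only self-reported data".
- Section 5.1 marks the second primary outcome with both: "Age at first major adverse cardiovascular event bs . Earliest of". The five components are first admissions for coronary, peripheral vascular, stroke and heart failure events, and "Age at cardiovascular death".
- Section 5.2 (Components of the Primary outcomes) lists the fatal component alone as "Age at cardiovascular death b" and "Proportion with cardiovascular death b". Both carry b without s.
- Section 5.2 (Win Ratio Secondary Outcomes) lists a time-to-MACE outcome that leaves out cardiovascular death. It carries b and no s.
- Section 10 gives the purpose: "An aim of this research program is to compare outcomes based on expert clinical synthesis of administrative and self-reported data" with outcomes taken from the questionnaire alone. It calls the analysis complementary and relies on the questions closest to each listed outcome.
- The results go to Supplementary Table 1, "Primary outcomes based on self-reported questionnaire only", and Table 8 also has a questionnaire-only block among the sensitivity analyses.

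**The concern.** The plan marks a composite for self-report analysis although one of its components is not marked when it stands alone, and it attaches a denominator that questionnaire data cannot fill. The two MACE results will be read against each other, since Section 10 states that purpose and Table 8 places the questionnaire version among the sensitivity analyses. If they differ, a reader would tend to conclude that self-report captures events poorly. The same difference could arise because fatal first events are missing, because non-fatal events in people who died before the questionnaire are missing, or because responders are a selected part of the cohort. At stake is the interpretation of the source comparison for a primary outcome.

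**Working it through.** **1. The plan's own figure for this outcome.** Section 9 gives 420 participants, 8% with an event, hazard ratio 0.33, 5% significance and 90% power. Section 13 makes the tests two-sided. I assume a 1:1 split.

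- Events available: 0.08 × 420 = 33.6.
- Events needed (Schoenfeld): 4 × (1.960 + 1.282)² / (ln 0.33)² = 4 × 10.51 / 1.229 = 34.2, rounded up to 35.
- Power with 33.6 events: Φ(√(33.6/4) × 1.1087 − 1.960) = Φ(1.253) = 0.895.

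The stated 90% reproduces. The concern is not an error in that figure.

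**2. The two versions side by side.**

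| | Main version | Self-report version |
|---|---|---|
| Source | Clinical synthesis of administrative and self-reported data | Questionnaire only |
| Components | Five, including cardiovascular death | At most the four non-fatal ones |
| People | Everyone alive at 28 days (b) | Living people who completed the questionnaire |
| Fatal first event | Counted | Absent |
| Non-fatal event, death before the questionnaire | Counted | Absent |

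Only the first row is the contrast that Section 10 wants. The other rows differ for reasons unrelated to the accuracy of self-report.

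**3. The denominator.** Section 5 gives no separate denominator for the self-report analyses, and Section 10 speaks only of all participants. If b were applied literally, people without a questionnaire would have to be either left out or counted as event-free. These choices can give different hazard ratios. Section 8 (subsection numbered 4.3) rules out imputation but does not choose between them.

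The documents give a rough bound on the population gap. Section 3.5 reports 534 offspring followed up at about 30 years, all of whom belong to denominator b. If 420 stands for the number who can answer the questionnaire (an assumption; Section 9 ties the sample size to those who can be located), responders are at most 420 / 534 = 79% of denominator b. The full size of b is not given, so the true share may be lower.

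**4. Illustration of the lost fatal events.** The SAP gives no count of fatal first events. For an assumed share of 33.6 events:

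| Assumed fatal share | Events absent | Events left | Power at HR 0.33 |
|---|---|---|---|
| 10% | 3.4 | 30.2 | 86.2% |
| 20% | 6.7 | 26.9 | 82.0% |
| 30% | 10.1 | 23.5 | 76.7% |

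This shows direction only. The shares are assumed, the base is 420 instead of denominator b, and non-fatal events in people who later died are not included.

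**The case against.** The other side has several good points.

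- **Death is probably dropped already.** Section 10 uses the closest questions, which implies a non-fatal self-report MACE. A reader might infer from the s mark in Section 5.1 that the plan keeps cardiovascular death in the self-report version; the SAP does not say so. This stands, but it leaves the mismatch in place: the self-report version then has at most four components and its comparator still has five.
- **Supplement S1 may define it.** Section 5 places outcome definitions and the hierarchy of data sources there, and S1 is not shown. No claim can be made that S1 is silent. The denominators, however, are assigned in the SAP itself, and the conflict between the marks is visible there.
- **A non-fatal MACE is already planned.** True, but it has no s mark, uses denominator b, and appears in Table 4 as a win-ratio component. It supplies the definition, not a comparison in the same people.
- **The elements can be compared singly.** All four non-fatal elements carry b and s in Section 5.2 as age at first admission. A reader might infer that the aim of Section 10 cannot be met for MACE at all; that goes too far. These single outcomes have no fatal component, though they share the denominator problem.
- **The analysis is complementary.** This stands and limits the weight of the point.
- **The reason for the missing s is not given.** Some other outcomes lack it too, such as the proportion with a heart failure admission. The argument needs only the marks as they are, and the fact that the questionnaire is completed by the participant.

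**Conclusion.** The point holds in a limited form. The s mark is on a composite whose fatal component the plan does not mark for self-report, and denominator b cannot apply to questionnaire data. As written, a gap between the two MACE hazard ratios cannot be attributed to data source, so the comparison is confounded for the composite. It is repairable with data already to be collected.

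The documents do not support any doubt about the main primary MACE analysis, its power statement or its inference; none of these depends on the self-report version. Nor do they support a firm count of missing events: the 3 to 10 in the illustration rest on an assumed 10–30% fatal share of 33.6 events. Bias by treatment arm would arise only if treatment affected fatal events or response, on which the SAP gives no data. The conclusion itself rests on the marks and denominators in Section 5 and on one premise: only living people answer the questionnaire.

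**What to change.** 1. In Section 5.1, remove the s mark from the full MACE composite. Keep that composite, with cardiovascular death and denominator b, as the primary outcome.
2. Move the s mark to the MACE outcome without cardiovascular death already listed in Section 5.2, and label the self-report result as non-fatal in Supplementary Table 1 and Table 8.
3. Set questionnaire responders as the denominator for the self-report version, and apply the same denominator to the self-report versions of the other outcomes marked b and s in Section 5.2.
4. For the source comparison, recompute the clinical-synthesis non-fatal MACE in exactly those responders. Report the two hazard ratios side by side, with a cross-tabulation of who is a case by each source.

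The cost is SAP wording and one extra model on data already held. The self-report result will have somewhat fewer events (the number cannot be derived from the SAP) and will apply only to survivors who responded. It therefore serves the comparison of sources and does not replace the treatment comparison in denominator b.

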#### 5.2. Secondary outcomes

##### **Components of the Primary outcomes**

- Diabetes mellitus or prediabetescs
- Diabetes mellituscs
- Prediabetescs
- Hypertensioncs
- Dyslipidaemiacs
- Age at cardiovascular deathb
- Proportion with cardiovascular deathb
- Age at first admission for myocardial infarction or coronary revascularisationbs
- Age at first admission for myocardial infarctionbs
- Age at first admission for coronary revascularisationbs
- Age at first admission for peripheral vascular disease (arterial thrombosis/embolism or need for revascularisation)bs
- Age at first admission for arterial thrombosis/embolismb
- Age at first admission for peripheral revascularisation procedureb
- Age at first admission for strokebs
- Age at first heart failure admissionbs
- Proportion with at least one admission for myocardial infarction or coronary revascularisationbs
- Proportion with at least one admission for myocardial infarctionbs
- Proportion with at least one admission for coronary revascularisationbs
- Proportion with at least one admission for peripheral vascular disease (arterial thrombosis/embolism or need for revascularisation)b
- Proportion with at least one admission for arterial thrombosis/embolismb
- Proportion with at least one admission for peripheral revascularisation procedureb
- Proportion with at least one admission for strokebs
- Proportion with at least one admission for heart failureb

### **Win Ratio Secondary Outcomes**

- Hierarchical win ratio outcomea: 6 step, unmatched, win ratio hierarchy including time to death after randomisation; time to first major adverse cardiovascular event; diagnosis of diabetes mellitus; number of admissions to hospital with respiratory illness as primary reason for admission; self-reported general health; time in hospital per 10 years alive after 1988
- Components of the win ratio outcome
  - Time to death after randomisationa
  - Time to MACE (excluding cardiovascular death)b
  - Diagnosis of diabetes mellitus (excluding prediabetes)c
  - Number of admissions to hospital with respiratory illness as primary reason for admission (admissions per patient year)b
  - Self-reported general healthc
  - Time in Hospital per 10 years alive after 1988b

### **Additional Secondary Outcomes**

- Ischaemic heart diseasecS
- StrokecS
- Peripheral vascular diseasec
- Overweight or obesitycS
- BMI (continuous)cS
- Death from any causea
- Self-reported general healthcS
- Rate of admissions to hospital with respiratory illness as the primary reason for admission/per patient year of followupc
- Chronic respiratory illness (Self-reported diagnosis of asthma or COPD, self-reported chronic respiratory symptoms, admissions for asthma or chronic obstructive pulmonary disease [COPD] or prescription of pharmaceuticals for asthma or COPD)c
  - AsthmacS
  - COPDcS
  - Chronic respiratory symptomscS
  - Admissions for asthma or chronic obstructive pulmonary disease (COPD)c
  - Prescriptions of pharmaceuticals for asthma or COPDc
- Highest level of educational attainmentcS

### **5.3. Tertiary Outcomes**

#### **General health outcomes**

- Functional difficultiescS
- Physical activity (categorical)cS

#### **Other Diabetes outcomes**

- Type 2 diabetes mellituscS
- Type 1 diabetes mellituscS
- Gestational diabetes mellituscS

#### **Other Cardiovascular outcomes**

- Heart failurecS
- Atrial fibrillationcS

**Reproductive system outcomes: Male**

- Number of babies  $\geq 20$  weeks' gestation fatheredcS

**Reproductive system outcomes: Female**

- Age at menarchecS
- Number who have reached menopause and age at menopausecS
- Need for assisted reproductive technologycS
- Polycystic ovarian syndromecS
- Total number of pregnancies  $\geq 20$  weeks (parity)cS

**Mental health Outcomes**

- Diagnosis or treatment of a mental health disorderc
- DepressioncS
- Bipolar affective disordercS
- Anxiety disordercS
- SchizophreniacS
- Inpatient admission for a mental health disorder (excluding mental disorders due to known physiological conditions)c
- Prescriptions of pharmaceuticals for mental health disorderscS

**Other health outcomes**

- Total number of fracturescS
- Cancer diagnosiscS
- Allergic condition other than asthma (diagnosis of or prescription of treatments for allergic conditions)cS
- Chronic kidney diseasec
- Self-reported oral healthcS
- Number of teeth removed for decaycS

**Social Outcome**

- Any court charges or convictionsc
- Employment statuscS
- Proportion with tertiary qualificationscS
- No secondary school qualificationcS

## 6. Outcome reporting

Outcomes may not all be reported in the same publication, instead being grouped into categories for reporting. These categories will likely include cardiometabolic and respiratory outcomes, other health outcomes and socioeconomic outcomes.

## 8. General issues for statistical analysis

### 4.1. Analysis software

All analyses will be performed using SAS® software version 9.4 (SAS Institute Inc., Cary, NC, USA).

#### 4.2. Analysis approach

Analyses will be performed using an intention-to-treat approach with participants analysed according to the initial treatment group to which their mother was allocated. Denominators have been indicated above for each study outcome.

#### 4.3. Approach for withdrawals, missing data and outliers

Data up to the point of withdrawal will be used for those participants who have withdrawn from the study unless they have withdrawn their consent for use of their data. No imputation will be performed for missing data. We do not plan to exclude outliers from the analysis. Sensitivity analyses will be performed to assess the impact of missing data on the primary and secondary outcomes.

#### 4.4. Protocol deviations

Participants will be included in the intention-to-treat analysis, regardless of protocol deviations. A small number of women were randomised more than once within the same pregnancy. These pregnancies will be analysed in the group to which they were first randomised.

#### 4.5. Covariates and potential confounders

Adjusted and unadjusted results will be presented for all outcomes. The results will be adjusted based on the following variables. Additional baseline variables will be included in the model if these differ markedly between treatment groups and are known to influence the particular outcome.

- Gestational age at randomisation (continuous variable)

